## List of abbreviations and definition of terms

ACS – Acute Coronary Syndrome  
AE - Adverse events  
AEIH – Albert Einstein Israelite Hospital  
AMI – Acute myocardial infarction  
CEC – Clinical Events Committee  
CI –Confidence Interval  
CRF – Case Report Form  
DBP – Diastolic Blood Pressure  
DD – Double Dose  
ECG – Electrocardiogram  
FICF – Formulary of Informed Consent Form  
GBS – Guillain-Barré Syndrome  
HD – Higher Dose  
HR – Hazard Rate  
ITT – Intention to Treat  
MACE – Major Adverse Cardiovascular Events  
OR – Odds Ratio  
PASS – Power Analysis Sample Size  
PP – Per protocol  
RMST - Restricted Mean Survival Time  
RR – Relative Risk  
RRR – Relative Risk Reduction  
SAP – Statistical Analysis Plan  
SAS – Statistical Analysis System  
SBP – Systolic Blood Pressure  
SD - Standard Dose  
TIA – Transient Ischemic Attack  
VCA – Vascular Cerebral Accident  
WR – Win Ratio

[figure not shown][figure not shown]

## 1. INTRODUCTION

### 1.1. Background and rationale

Cardiovascular diseases impose a great burden in the context of public health, especially among patients with chronic non-transmittable diseases, who have low adherence to drug therapies. Vaccination with increased dose throughout the year could be a cost-effective intervention to reduce cardiovascular events, since it is an approach of easy adherence, administration and low cost, when compared to long-standing use of medications.

A prior study demonstrated that influenza vaccination during the acute phase after myocardial infarction (MI) led to a 28% relative risk reduction in the composite of death, recurrent MI or stent thrombosis, versus placebo. However, it remains unknown whether patients admitted with acute MI should be vaccinated soon after hospitalization, and whether a higher dose is more efficacious than standard dose vaccination. Therefore, a study evaluating high dose (HD) influenza vaccination in a period that contemplates the seasonality of the influenza virus in Brazil may bring important findings to different scientific gaps, as well as clarify questions about the possible benefit of double-dose vaccination, which does not present contraindications, immediately after an atherothrombotic event. If it shows real benefit, it may also be a future adjunctive therapy in the prevention of cardiovascular events.

### 1.2. Objectives

#### Primary objectives

To assess whether increased doses of influenza vaccine in the hospital phase, when compared to usual dose vaccination, reduce the risk of major cardiovascular and respiratory complications in patients with acute coronary syndrome, within 12 months of follow-up.

**Hypothesis:** A double dose influenza vaccination during the hospitalization phase of patients with ACS is superior in preventing cardiorespiratory events or death, compared with single dose 30 days after randomization.

[figure not shown]

## Secondary objectives

The secondary objectives aim to assess whether, within 12 months, in acute phase ACS patients, the increased dose influenza vaccine is superior to the routine outpatient procedure to avoid the following outcomes:

- All-cause death;
- Cardiovascular death;
- AMI (acute myocardial infarction);
- Stroke/transient ischemic attack (TIA)
- Hospitalization for unstable angina;
- Urgent myocardial revascularization;
- Non-urgent myocardial revascularization;
- Hospitalization for heart failure;
- Hospitalization for respiratory infection
- Hospitalization for COVID-19 or death for COVID-19;
- Stent thrombosis.

## Additional objectives

Assess whether there is an interaction between the effect of the vaccine in the acute phase and influenza season in the southern hemisphere.

Sub study objectives of immunogenicity, biomarkers and virology assessments

The VIP-ACS study will select centers in different regions of viral seasonality to evaluate:

- The correlation between the seroconversion to vaccination and the age of patients ( $> 65$ ,  $\leq 65$  years)
- Whether the increased seroconversion through the use of an increased dose of the vaccine may have implications for the primary outcome of the study.
- The correlation of the findings of the study to immune responses following vaccination, via cytokines, or other biomarkers.
- The correlation between the viral typing of the patients included in the study and the type of outcome, since certain viral subtypes may be more immunogenic.

[figure not shown]

## 2. STUDY METHODS

### 2.1. Trial Design

A randomized controlled, open-label, multicenter, superiority, parallel group and 1:1 allocation trial, with blind assessment of clinical outcomes.

After evaluation of an acute coronary syndrome (ACS) confirmed by exams, and during hospitalization phase, if the patient attends to the enrollment criteria and signs the consent form, the randomization to one of the vaccination arms of the study will occur.

The patient can be randomized to one of the following arms:

- 1) Double-dose influenza vaccination (DD) – administered during the hospital stay phase, as early as possible following randomization
  - 2) Standard dose influenza vaccination (SD) – administered  $30 \pm 5$  days after randomization
- Subsequently to the randomization date, each patient will be followed for 12 months, for the monitoring of cardiovascular and respiratory events.

The study was planned to initiate the randomizations from the availability of the 2019 influenza vaccine (March 2019) and continue until November 2020, even beyond the national influenza immunization campaign period for those years. Despite the effort made to completion of the planned inclusion sample, ensuring the representativeness of both planned influenza periods, the first recruitment period was impaired due to regulatory delays in the study initiation. Since the beginning of the second recruitment period, the protocol was amended (version 4, of 04-Jul-2020), the study sample size was recalculated as an event-driven study, and the timing of final analysis was set as the date when 953 primary efficacy outcome events would have occurred, even if it was necessary to continue recruitment through the year 2021.

In 2020, the COVID-19 pandemic impacted recruitment and conduct of the trial. First of all, national influenza vaccination campaign was anticipated and the adherence to immunization was higher than before, making fewer patients eligible for the study during this recruitment period. Second, enrollment was hurdled because patients were constrained of returning to study in-person visits to receive the outpatient vaccination, should they have been assigned to the control group. Due to those issues, the study steering committee decided to end recruitment after 1,800

[figure not shown][figure not shown]

patients from an initial sample size of 9000 have been enrolled. This decision was made without any knowledge of data comparing the study groups by the steering committee or by external independent committee. At that time, the sample size was recalculated, changing the analytical method of the primary endpoint from a z-test with first event from a composite outcome to a Win Ratio approach, and including all-cause mortality and hospitalization for respiratory infections (excluding COVID-19) in the primary endpoint. With the participants enrolled at the time and considering the aggregated reported event rates, the study would preserve a power of > 80% for detecting a relative risk reduction of 28% in the components of the primary endpoint, therefore compatible with a recently published randomized trial in the field and a meta-analysis of previous trials suggesting that magnitude of effect as being plausible and clinically relevant. After this decision, the protocol was amended (version 6.0, of 20-Oct-2021) and a new version of the statistical analysis plan was drafted.

## 2.2. Randomization

The randomization was performed through the electronic CRF, using the HIAE Data Management System, which was validated by previous studies, presenting safety and reliability for the VIP-ACS study. The randomization list of patients was generated considering a random function with equal probability of allocation to one of the vaccine therapies groups, stratified by research center, using blocks of 8, 10 and 12. Each vaccination arm was numbered and only the numbers were used in the randomization, which was done by the central electronic randomization of the project's coordinating center in the HIAE, ensuring the concealed allocation.

This is an open-label study in which researchers, health care workers and patients are aware of the treatment allocation. All clinical outcomes were evaluated and validated by an Independent Clinical Events Committee, whose members were blinded to the study arm assignments.

[figure not shown][figure not shown]

**Figure 1.** Randomization scheme and follow-up of the VIP-ACS study. ACS = acute coronary syndrome; DD = Double dose of vaccine; SD = Standard dose; V1 = visit 1; V2 = visit 2; V3 = visit 3; VS 1 = visit for safety 1; VS 2 = visit for safety 2; mo= months.

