| Steering Committee     | [name] (Chair, Co-PI), [name] (Co-PI) [name]; [name]; [name]; [name]; [name]; [name]                                                                                                                                                                                               |
| Predicted duration     | Approximately three years: February 2019 to December 2021.                                                                                                                                                                                                                                                                                                                                   |
| Sites                  | Approximately 30 sites in Brazil.                                                                                                                                                                                                                                                                                                                                                            |
| Study Design           | Randomized, prospective, active-controlled, open label, superiority clinical trial, with 1:1 allocation, blind assessment of clinical endpoints.                                                                                                                                                                                                                                             |
| Methodological Quality | Central randomization via web and confidential allocation; blind committee to evaluate and validate diagnostics and endpoints, intention-to-treat analysis.                                                                                                                                                                                                                                  |

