### **3.3 Randomization Method and Confidential Allocation**

The patients' randomization list will be generated considering a random function with equal allocation probability to one of the vaccine therapy groups and in relation to each investigational site. Each study vaccine group will be numbered and only the numbers will be used in the randomization, which will be performed through a randomization central electronic system of the project coordinating site at HIAE, guaranteeing the secrecy of the allocation. In special cases, where randomization problems occur, the coordinating site will contact the investigational site with the actions to be taken.

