## **5.2. Analysis methods**

Primary efficacy outcome: The analysis of primary efficacy endpoint—a hierarchical outcome consisting of all-cause death, MI, stroke, hospitalization for unstable angina, hospitalization for heart failure, urgent coronary revascularization or hospitalization for respiratory infection (excluding COVID-19) will be the comparison between the two arms using the unmatched win ratio method (refer to section 2.3).

Secondary key efficacy outcome: The secondary key outcome is defined also as a hierarchical outcome of CV death, MI, or stroke, in that order, and will be compared with the Win Ratio statistic using the same definitions for the primary endpoint.

Secondary efficacy outcomes: The analysis of the secondary efficacy endpoints, defined as time to first event of: All-cause mortality, Mortality from cardiovascular causes, Myocardial infarction, Stroke, Hospitalization for unstable angina, Need for myocardial revascularization (urgent and non-urgent), Hospitalization for heart failure, TIA (Transient ischemic attack), Hospitalization for respiratory and pulmonary infections, Hospitalization for COVID-19, and Stent thrombosis; will be tested using Cox proportional hazard models. All the effects statistic

[figure not shown]

will be Hazard Ratio (HR) between the two arms within 12 months, and corresponding 95%CI will be provided. Underlying assumptions of the Cox Proportional Hazard Model will be checked using graphical methods

The estimates of time to the first event (median time of event-free) will be also computed if possible, and Kaplan-Meier curves will be displayed, by treatment arm. Additional efficacy outcomes (Influenza season in the southern hemisphere): the prevalence of each strain within of the subtypes circulating in each season and location will be described in tables using proportions and graphically. The proportions will be compared using comparison of proportions tests.

Safety Outcomes: The number of patients having local and systemic adverse events up to 7 days after vaccination will be described by group and overall. The number of patients having any vaccination adverse event will be computed, and the 95% CI will be presented.

All the adverse events will be listed, by patient.

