### **5.5 Subgroup analyses:**

As many of the baseline characteristics are known to be prognostic for the clinical outcomes in the study population with high-risk cardiovascular disease (as sex, age group, race/ethnicity, smoking status, etc.), internal consistency of the primary analysis will be assessed in subgroups defined by these and other baseline characteristics.

Heterogeneity of efficacy will be assessed using interaction tests of treatment by each of these baseline covariates and by influenza season (Period), using the same aforementioned models.

The following subgroups will be prespecified in this SAP:

- Male vs. females;
- Age  $\geq$  vs. < 60 years;
- ACS presentation: (STEMI, NSTEMI, unstable angina)
- Diabetes vs. no diabetes;
- Smokers vs, non-smokers
- White race vs. non-white
- Killip class 2 or more vs. Killip class 1
- Previous heart failure vs not;
- Previous MI vs not;
- Previous stroke vs. not;
- Previous PCI vs not;
- Previous CABG vs not;
- History of chronic lung disease vs not;
- Prior COVID-19 vs.not.

[figure not shown]

- Time from presenting ACS to randomization (in tertiles)
- Time from hospitalization to randomization (in tertiles)
- Influenza season (Mar-Jul vs. other months);
- Enrollment year (2019 vs. 2020);
- Regions of the country (North and Northeastern vs others)
- COVID-19 vaccination vs not-vaccination.

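### Randomization is stratified by center and baseline factors are called prognostic, but no planned win ratio or Cox comparison of the arms names either: a small loss of power, not a validity error

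*Combined protocol and SAP*

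**What the plan says.** **Randomization.** SAP 2.2 states that the list was "stratified by research center, using blocks of 8, 10 and 12". Protocol 3.3 agrees: equal allocation probability was set "in relation to each investigational site". The protocol synopsis gives "Approximately 30 sites in Brazil".

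**Primary and key secondary outcomes.** SAP 5.2 states that the primary analysis "will be the comparison between the two arms using the unmatched win ratio method (refer to section 2.3"). Under SAP 2.3, each intervention patient is paired with each control patient, whatever the site. The key secondary outcome uses the same method.

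**Other outcomes.** The time-to-first-event secondary outcomes "will be tested using Cox proportional hazard models" (SAP 5.2). SAP 5.3 adds Cox models for the primary and key secondary composites, and protocol 6.2 also plans Cox models. None of these sections, nor SAP 5.4, names site strata or covariates.

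**Baseline factors.** SAP 5.5 opens: "As many of the baseline characteristics are known to be prognostic for the clinical outcomes in the study population with high-risk cardiovascular disease". It gives sex, age group, race or ethnicity and smoking status as examples. The stated use is subgroup consistency: "Heterogeneity of efficacy will be assessed using interaction tests of treatment by each of these baseline covariates". SAP 5.3 lists no stratified or covariate-adjusted sensitivity analysis, and no reason is given.

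**The concern.** When randomization is stratified, the usual practice is to let the analysis reflect the strata. When baseline variables predict outcome and are already collected, using them normally raises power. This plan has both ingredients and uses neither in its main comparisons.

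The trial has little power to spare. The sample was cut from about 9,000 to 1,800, and SAP 2.1 justifies this by power above 80%. Recruitment is closed, so the analysis is one of the few places where power can still be recovered. Silence about Cox covariates also leaves their choice open until comparative data can be seen.

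**Working it through.** **Inputs from the documents.** 900 patients per arm; two-sided 5%; 12 months of follow-up; independent events; exponential times; about 30 sites; blocks of 8, 10 and 12 within site. Control rates and absolute reductions are from the tables in SAP 2.3:

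| Component | Control % | Reduction % |
|---|---|---|
| Death | 7.0 | 2.0 |
| MI | 3.4 | 0.9 |
| Stroke | 1.0 | 0.3 |
| Unstable angina | 2.7 | 0.8 |
| Heart failure hospitalization | 2.9 | 0.8 |
| Urgent revascularization | 0.6 | 0.2 |
| Respiratory hospitalization | 1.0 | 0.3 |

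**Assumed, because the documents do not give them:** site sizes, between-site variation in risk, and the strength of the baseline factors.

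**Step 1: the plan's own figure.** In 10,000 simulated trials with a valid patient-level variance, the win ratio is 1.408, matching the protocol's 1.41. Power is 79.1%, against the stated 82.6%. A hand check on any-event risk agrees:
- Control: 1 − (0.930 × 0.966 × 0.990 × 0.973 × 0.971 × 0.994 × 0.990) = 0.1731.
- Intervention: 1 − (0.950 × 0.975 × 0.993 × 0.981 × 0.979 × 0.996 × 0.993) = 0.1263.
- Pooled risk 0.1497; SE = √(2 × 0.1497 × 0.8503 / 900) = 0.01682.
- z = 0.04676 / 0.01682 = 2.78; power = Φ(2.78 − 1.96) = 79.4%.

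The stated 82.6% is therefore not reproduced. Results below are shown from both starting points.

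**Step 2: converting efficiency to power.** Information gain g = (mean z with adjustment / mean z without)². Power = Φ(ncp × √g − 1.96), with ncp = 1.96 + 0.938 = 2.898 for 82.6% and 1.96 + 0.810 = 2.770 for 79.1%.

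**Step 3: site strata only** (30 equal sites, 400 trials per setting).

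| Between-site SD, log hazard | g, win test | g, Cox | Win-test power from 79.1% | Win-test power from 82.6% |
|---|---|---|---|---|
| 0 | 0.997 | 0.997 | 79.0% | 82.5% |
| 0.3 | 1.008 | 1.010 | 79.4% | 82.9% |
| 0.5 | 1.036 | 1.038 | 80.5% | 83.9% |

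A second simulation gave mean z of 2.74 both ways with no site effect, 2.66 rising to 2.67 at SD 0.3 (log risk), and 2.61 rising to 2.66 at SD 0.5. Those are g = 1.00, (2.67/2.66)² = 1.008 and (2.66/2.61)² = 1.039. A third, with unequal sites, gave 76.0% rising to 76.7% at log-odds SD 0.5, and 70.8% rising to 72.3% at SD 0.7.

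**Step 4: a baseline risk score** (unequal sites, site SD 0.3, 400 trials per setting).

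| c-statistic of score | g, win test with score | g, win test with score and site | g, Cox with score | Win test with score: power from 79.1% | from 82.6% |
|---|---|---|---|---|---|
| 0.65 | 1.047 | 1.059 | 1.049 | 80.9% | 84.3% |
| 0.72 | 1.090 | 1.103 | 1.104 | 82.4% | 85.7% |
| 0.77 | 1.115 | 1.122 | 1.167 | 83.3% | 86.5% |

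Across runs and methods the gain was roughly 3–5%, 9–10% and 11–15% at these c-statistics. The Cox entry of 1.167 lies just above that range. Multiplied by 1,800, the ranges equal about 50–90, 160–180 and 200–270 extra patients. A separate simulation of score adjustment gave about 2 points (76.1% to 78.0%, and 71.3% to 73.4%).

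**Step 5: where the Cox gain comes from** (c = 0.72).
- Unadjusted: HR 0.724, SE 0.1275; z = ln(0.724)/0.1275 = −2.53.
- Score-adjusted: HR 0.712, SE 0.1276; z = −2.66.
- Adjusted and site-stratified: HR 0.709, SE 0.1286; z = −2.67.

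The ratio (2.66/2.53)² is about 1.10. All of it comes from the log hazard ratio moving further from 0; the standard error does not fall.

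**Step 6: validity.** With a valid variance, the simulations showed no sign that omitting site inflates the type I error.

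**The case against.** The strongest reply is that nothing here is an error. An unmatched win ratio is a legitimate choice, the unadjusted hazard ratio estimates a legitimate marginal quantity, and adding strata and covariates is a matter of preference. Much of this stands, and it limits the point in five ways.

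- **Site.** A reader might infer that ignoring the strata invalidates the test or costs much power. Neither is supported. The gain is close to zero unless sites differ strongly, and stratification can cost a fraction of a percent when they do not.
- **Precision.** A reader might call adjustment free precision. For Cox that is wrong: the standard error does not shrink, and the hazard ratio becomes conditional, a different estimand.
- **Silence.** The SAP does not say that the Cox models contain treatment only. It names no covariates, which is an omission and not a stated exclusion.
- **Which factors.** Among the examples SAP 5.5 gives of prognostic factors, only age group overlaps with the covariates suggested below. Index ACS type, Killip class, prior MI, heart failure and diabetes appear there as subgroups. Their strength here is unknown.
- **Order of repair.** The z formula in SAP 2.3 treats every pair as independent. Used with all pairs, it rejected a true null in about 94% of simulated trials. Remarks about a pooled test being valid or slightly conservative do not apply to that formula.

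The efficiency point survives: the strata and the baseline data exist, the plan does not use them in its main comparisons, and using them is cheap.

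**Conclusion.** The point holds as a minor improvement. The planned comparisons do not reflect the stratified randomization and leave collected baseline information unused. Site stratification is worth about 0 to 1 power point, or about 1.5 when sites differ strongly. Covariates are worth about 1 to 5 points, and most of the possible gain lies there. These figures assume a between-site SD of 0 to 0.5 on the log-hazard scale (0.7 on the log-odds scale at the extreme) and a score with a c-statistic of about 0.65 to 0.77. They also assume complete 12-month follow-up.

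The documents do not support a claim that the comparison is biased or invalid because strata are ignored. The gap between 79.1% and 82.6% is a separate matter; the gain is similar from either base.

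**What to change.** First correct the variance in SAP 2.3. Then, before unblinded analysis, amend SAP 5.2 to 5.4 as follows:

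1. **Primary and key secondary outcomes.** Test with patient-level Finkelstein-Schoenfeld scores, stratified by randomizing site. State a rule for merging very small sites within region. Adjust for a short fixed list of collected baseline covariates, for example age, index ACS type, Killip class, prior MI, heart failure and diabetes. Confirm that Killip class was recorded: it is a subgroup in SAP 5.5 but is not listed in SAP 4.5.
2. **Cox models.** Stratify by site, adjust for the same list, and label the hazard ratio as conditional.
3. **Sensitivity analyses.** Keep the pooled win ratio and the unadjusted hazard ratio.

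The cost is SAP wording and standard code, with no new patients, data or procedures. The downsides are the need for a merging rule and a conditional hazard ratio. A patient-level score test with its own variance would also replace the pairwise formula, so one rewrite can serve both problems.
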